### Assignment of interventions

2.10

#### Allocation

2.10.1

##### Sequence generation, concealment mechanism, and implementation

2.10.1.1

The principal investigator (DR) will oversee the screening procedure (i.e., contacting with patients and performing Visit 1). The randomization process will be centralized electronically using the e-CRF itself (research electronic data capture software [REDCap] platform) the day before the surgery. The randomization list will be computer-generated in blocks of 4. Patients will be assigned to the study groups at the time of enrollment on the study.

The randomization to the type of cemented stem prosthesis studied will be blinded to the participant and the surgeon team until the day of the surgery.

#### Blinding (masking)

2.10.2

After assignment to interventions (Exeter V40 cemented femoral stem or Müller straight stem), both participant and surgical team will be aware of the type of cemented stem prosthesis allocated. Since after randomization this becomes an open-label study, emergency unblinding does not apply. Data analysts will be blinded.

Personal patient data will be coded and dissociated, so that the patient to whom they correspond is not recognizable. Consecutive numbers will be assigned as they are enrolled in the study, and these numbers (or codes) will be used in the electronic case report form (eCRF), rather than personal data.

### Data collection plan

2.11

All data will be gathered from electronic medical records during the trial. All patients on the waiting list for total hip arthroplasty surgery during the study period will be screened and enrolled, if they meet the inclusion criteria and accept to participate, until reaching a total of 16 patients.

The study team will gather information on demographic characteristics, such as age and gender; body mass index; pathological background, particularly diabetes mellitus, hypertension, renal failure and vascular disease; preoperative anesthetic risk assessment (i.e., American Society of Anesthesiologists’ classification scale of overall physical health); clinical diagnosis that justify the surgical procedure indication; surgical approach; type of cemented stem prosthetic and its cementation; treatment with bone density altering drugs, such as corticosteroids or bisphosphonates, prior to the surgery; date of the intervention; date of hospital discharge; postoperative complications; pre- and postoperative clinical and radiographic assessment scales (i.e., the Harris and Merle d’Aubigne Scores, the WOMAC Index, the EuroQoL-5D-3L© questionnaire and the Harris Radiographic Classification of Loosening Risk).

The Harris Hip Score considers 4 clinical domains: pain, function, range of motion, and absence of deformity. Pain adds a maximum of 44 points; function, 47 points; range of motion, 5 points; and absence of deformity, 4 points. The maximum score is 100 points (best possible result), and the minimum is 0 (worst possible result)[^12^,^13^] (see Table S1, Supplemental Digital Content).

The Merle d’Aubigné Score considers pain, walking, and mobility. It is classified as “Very good”, “good”, “average”, “reasonable” and “poor”, according to pain and walking scores, and adjusted down 1 to 2 grades, according to the mobility score[^12^,^14^] (see Table S2, Supplemental Digital Content).

The WOMAC Index considers 3 different domains: pain (5 questions), stiffness (2 questions), and function (17 questions). The combined scores range from 0 to 96, being 96 the best possible result and 0 the worst possible result^[15]^ (see Table S3, Supplemental Digital Content).

The EuroQoL-5D-3L© questionnaire (EQ-5D-3L) was introduced in 1990. It is one of the most widely used instruments for measuring health-related quality of life. The EQ-5D-3L essentially consists of 2 pages: the EQ-5D descriptive system and the EQ-5D visual analogue scale (EQ VAS). The EQ-5D-3L descriptive system comprises the following 5 dimensions, each describing a different aspect of health: mobility, self-care, usual activities, pain/discomfort, and anxiety/depression. Each dimension has 3 levels: no problems, some problems, extreme problems (labelled 1-3). The respondent is asked to indicate his/her health state by checking the box against the most appropriate statement in each of the 5 dimensions.^[13]^ The EQ VAS records the respondent's self-rated health on a vertical VAS where the endpoints are labelled “The best health you can imagine” and “The worst health you can imagine”. This information can be used as a quantitative measure of health outcome as judged by the individual respondents^[16]^ (see Table S4, Supplemental Digital Content).

Permission for EuroQoL-5D-3L© questionnaire's use on this trial and for its reproduction on future related publications has been granted by the EuroQoL Office.

Harris radiographic classification of loosening risk is based on defined radiographic criteria and classifies the risk of stem loosening. The presence of a radiolucent line of 50% to 100% of the cement-bone boundary is defined as “possibly loose”. Radiolucency at 100% of this limit is classified as “probably loose”. Stem migration or a fracture of the cement mantle is classified as “definitely loose”. The more progressive the radiological lines, the more likely it is that there will be a prosthetic loosening[^10^,^11^] (see Table S5, Supplemental Digital Content).

SPECT-CT results will be recorded in the eCRF. Measurements on the prosthetic stem area will be performed considering 12 standard zones. SPECT results will be expressed as “counts per image set” (i.e., photons that represent the radiopharmaceutical uptake by the gamma camera) and as Standardized Uptake Values (SUVs) from each predetermined study areas.[^8^,^17^]

Quantification of periprosthetic activity will be performed by applying regions of interest, segmenting the areas in both the acetabular and femoral components. CT-scan results will provide data on bone density. The “comparative ratios” between the predetermined study area and its homologous contralateral counterpart will also be obtained. Early phase measurements will provide soft tissues’ activity information, and late phase measurements will provide information on bone formation.

An eCRF based on the REDCap platform (REDCap Consortium), has been created ad hoc for this study in coordination with the Biostatistics Unit of the IDIBELL and does not collect data that allows patient identification. Once the study is completed, the information collected will be transcribed into an anonymized ad hoc created database, which will be used for further statistical analysis.

### Plans to promote participant retention and complete follow-up

2.12

Participants’ follow-up will be the same as for other patients not enrolled in this trial, except for the SPECT-CT scan that will be performed on post-operative months 3, 6, 12, and 24 after surgery. In other words, the Participants’ follow-up is the same to our clinical practice, except for SPECT-CT. This additional complementary imaging test will be carried out within the scope of the Bellvitge University Hospital, on the programmed clinical follow-up visit day and will not incur on extra expenses of any kind for the patients.

In each face-to-face medical follow-up visit, the clinical investigator in charge will remind the patient of the importance of correctly following the study and will encourage them to carry on in the clinical trial.

Protocol deviations will be documented and explained in detail by the investigators team (the sponsor is the principal investigator of this team). In the event of a “serious” protocol violation, the monitoring team will record all protocol breaches/deviations. The sponsor will review all protocol deviations and assess whether any of them represent a “serious” violation according to Good Clinical Practice guidelines. The sponsor will inform the IRB of any protocol breach/deviation that could impact on patient safety and on data integrity.

### Data management

2.13

An electronic case report form (e-CRF), based on REDCap platform (REDCap Consortium), will be created ad hoc for this study in coordination with the Biostatistics Unit of the IDIBELL. It does not collect data that allows patient identification.

Before closing the database for analysis, the data manager and the principal investigator will check the completeness and accuracy of the recorded data. We do not expect confounding factors to influence the results, since this is primarily a descriptive study.

### Statistical methods for analyzing primary and secondary outcomes

2.14

Baseline characteristics, type of surgery and its indication will be described using standard descriptive methods, and a descriptive and exploratory comparative analysis between both study groups will be carried out. The results will be expressed as means and standard deviation, median (maximum and minimum values) for the quantitative variables. Categorical variables will be expressed with the absolute and relative frequencies of each category.

Primary outcomes will be analyzed by determining the median (and its 95% confidence interval [95% CI]) of image-counts in the SPECT (to assess whether there are bone metabolic differences between the 2 types of cemented stem prostheses); and determining the median (and its 95% CI) of the alignment angles of the 2 types of cemented stem prostheses in plain radiography and CT scan (for morphological assessment).

Secondary outcomes will be analyzed by determining the median (and its 95% CI) of the axial displacement degree of the 2 types of cemented stem prostheses in plain radiography and CT scans; determining the median (and its 95% CI) of the interdigitation penetration range between the cement and the bone in the CT scans of both types of prostheses; calculating the proportion (and the absolute number) of patients classified as “possibly loose”, “probably loose” or “definitely loose” according to the radiographic fixation (loosening risk) of both types of prostheses in the plain radiography, according to the Harris Radiographic Classification of Loosening Risk[^10^,^11^]; determining the median Harris Hip Score (and its 95% CI),[^12^,^13^] pre- and postintervention, for both types of prostheses; determining the median Merle d’Aubigné Score (and its 95% CI),[^12^,^14^] pre- and postintervention, for both types of prostheses; determining the median WOMAC Index Score (and its 95% CI),^[15]^ pre- and postintervention, for both types of prostheses; determining the median EuroQoL-5D-3L© questionnaire score (and its 95% CI),^[16]^ pre- and postintervention, for the 2 types of prostheses.

Association studies will also be carried out. A 95% CI for the estimates shall be provided whenever it is possible.

Finally, the statistician who will perform the data analysis will be blinded regarding the study groups (Exeter V40 cemented femoral stem group or Müller Straight Stem group). R version 3.6.2 or higher for Windows (R Foundation for Statistical Computing) will be used for data processing and analysis.

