Nevertheless, an implant's insertion into the bone (in this case, the femur) generates bone mass and bone metabolism changes around the implant. Monitoring these metabolic changes, and, therefore, the peri-prosthetic bone reaction, is of great importance when evaluating the results of each prosthetic model. There are many methods for peri-prosthetic bone changes monitoring, such as plain radiography, computed tomography (CT) scan, magnetic resonance imaging, dual energy radiography absorption and single photon emission computed tomography (SPECT). SPECT with technetium 99-labeled methyl-diphosphonates (MDP) is a useful tool for bone metabolism assessment^[4]^ and, although this technique may show insufficient anatomical details, its combination with CT scan (SPECT-CT) provides a solution and allows a combined metabolic and morphological study.^[5]^

To our knowledge, there are no studies comparing bone metabolism evolution in the postoperative period between these 2 approaches (thick-layer cement vs “French paradox”) with SPECT-CT. The aim of this work is to provide information on bone metabolic activity in the postoperative period of these 2 femoral stem models and to determine whether there are differences between them.

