### Methods for any additional analyses

2.15

Additional analyses are not planned. Nevertheless, an exploratory multivariate regression model will be constructed and adjusted for potentially important confounding factors such as age, gender, clinical baseline characteristics.

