### Adverse event reporting and harms

2.19

Adverse events recorded during the study will be coded according to the latest available version of the MedDRA dictionary and will be described using absolute and relative frequencies by study group, according to severity and its causal relation with treatment.

Serious adverse events will be described by study group and the 95% CI of the difference between both groups will be calculated.

Regarding the SPECT-CT, we do not expect any adverse reactions, since it is extremely rare for radio-induced secondary effects to appear (given the low doses of the radiopharmaceutical received^[6]^). Nonetheless, any adverse event that may occur during the trial will be assessed by the study team and, should any adverse reaction be related to the radiopharmaceutical administered, it would be collected in detail and notified to the Catalan Pharmacovigilance System.

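### Section 2.14 sets out to assess whether the two stems differ but names only medians with their own intervals: no between-arm effect with a CI, and no adjustment of clinical scores for the preoperative value, is specified

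*Protocol article*

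**What the plan says.** The aim is comparative. Section 1.1 of the protocol article wants to describe metabolic activity after both stems and "to determine whether there are differences between them". Section 2.14 attaches that purpose to the primary metabolic analysis: "Primary outcomes will be analyzed by determining the median (and its 95% confidence interval [95% CI]) of image-counts in the SPECT", which is done "to assess whether there are bone metabolic differences between the 2 types of cemented stem prostheses".

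The other outcomes follow the same pattern. The second primary outcome is handled by "determining the median (and its 95% CI) of the alignment angles of the 2 types of cemented stem prostheses". Axial displacement and cement penetration get a median and CI as well. The clinical scores are treated by "determining the median Harris Hip Score (and its 95% CI"), "pre- and postintervention, for both types of prostheses", and Merle d'Aubigné, WOMAC and EQ-5D-3L are worded alike. Loosening risk is a count and proportion.

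Three other statements bear on the comparison:

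- Section 2.14 announces an exploratory comparative analysis of the groups, association studies, and a 95% CI for estimates where possible. It names no measure or method for these.
- Section 2.15 first says that no additional analyses are planned, then that "an exploratory multivariate regression model will be constructed and adjusted for potentially important confounding factors such as age, gender, clinical baseline characteristics".
- Section 2.19 does specify a contrast, for serious adverse events only: "the 95% CI of the difference between both groups will be calculated".

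**The concern.** Two separate medians with two separate intervals do not estimate how far apart the stems are or how uncertain that distance is. The authors specify a difference with a CI for serious adverse events but not for the question that the randomisation was set up to inform. As 2.14 stands, the reader is left to compare two intervals by eye, which is much less sensitive than a direct comparison of the same 16 patients.

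This matters more in a small pilot. Section 3 says that 16 is the most the budget allows and hopes to prepare larger studies. Those studies would need an effect estimate with an interval.

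The clinical scores raise a second issue. Table 3 collects them at Visit 1, and section 2.3 compares before with after. A stem-versus-stem comparison that uses each patient's own starting value is not specified, although chance imbalance at 8 per arm is often large.

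**Working it through.** **Inputs.** Section 2.8 gives 16 patients, 8 per arm. It states that no formal sample size calculation was made, so there is no power figure to reproduce. Normal data, equal SD, the true differences in SD units and the correlations below are assumptions, not figures from the protocol.

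**1. Distribution-free interval for one median, n = 8.** Coverage comes from the Binomial(8, 0.5) distribution.
- 2nd to 7th value: 1 − 2 × (1 + 8)/256 = 0.930.
- 1st to 7th (or 2nd to 8th) value: 1 − 1/256 − 9/256 = 0.961.
- Minimum to maximum: 1 − 2/256 = 0.992.

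**2. Direct comparison, 8 v 8.** The Mann-Whitney test that rejects at U ≤ 13 or U ≥ 51 has size 2 × P(U ≤ 13) = 0.0499. Inverting it gives the Hodges-Lehmann interval, with exact coverage 95.0%.

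**3. Reading two intervals against one direct comparison** (simulation, 100,000 runs per row):

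| True difference | Non-overlap, minimum-maximum | Non-overlap, 2nd-7th value | Mann-Whitney |
|---|---|---|---|
| 0 | 0.02% | 1.0% | 5.0% |
| 1 SD | 1% | 15% | 44% |
| 1.5 SD | 5% | 39% | 77% |
| 2 SD | 16% | 68% | 95% |

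Non-overlap of two minimum-maximum intervals requires complete separation of the arms. Its null probability is 2/12,870 = 0.00016, which agrees with the first row. The 1st-to-7th interval contains the 2nd-to-7th and lies inside the full range, so its non-overlap rate falls between those two columns.

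**4. Baseline score (clinical outcomes only).**
- Chance imbalance: the SE of a difference in baseline means is √(2/8) = 0.5 SD, so P(|difference| > 0.5 SD) = P(|Z| > 1) = 0.317.
- Variance with one baseline covariate, relative to no adjustment: (1 − r²) × 13/12, where 13/12 is the price of estimating the slope with 16 patients.
- r = 0.5: 0.75 × 13/12 = 0.81, a 19% reduction.
- r = 0.7: 0.51 × 13/12 = 0.55, a 45% reduction.
- Break-even: r² = 1/13, so r ≈ 0.28. Below that, adjustment costs a little precision.

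**The case against.** The strongest reply is that this is an exploratory pilot. Table 1 sets objectives to describe and to estimate, section 2.13 calls the study primarily descriptive, and a condensed article may leave the estimator and covariates to an analysis plan that is not shown. That is a good reason not to demand a confirmatory test or a full model specification. It does not remove the mismatch, because 2.14 itself chooses a method and says what it is for, and the method does not serve that purpose. An analysis plan could add the contrast, but the sentence in 2.14 would still need correcting.

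Several stronger readings are tempting, and the document does not support them:

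- *That no between-arm comparison will be made, or that preoperative scores will never be adjusted for.* Section 2.14 announces an exploratory comparison, and the baseline characteristics in 2.15 could include the Visit 1 scores. What can be said is that neither is specified.
- *That the plan will judge differences by CI overlap.* No section states such a rule. The non-overlap figures show what a reader could do with the named output, not what the authors intend.
- *That no distribution-free 95% interval for a median exists at n = 8.* Intervals with at least 95% coverage exist, at 96.1% and 99.2%. Section 2.14 does not prescribe the order-statistic method either.
- *That about ten covariates will be fitted.* Section 2.15 gives three examples, one of them a category. The list in 2.11 is for data collection.
- *That baseline adjustment would help the primary outcomes.* Table 3 has no preoperative SPECT-CT, and a preoperative film cannot show stem alignment.

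**Conclusion.** The point holds in this form: for the primary and quantitative secondary outcomes, the named analysis is a median with its own CI, no between-arm effect measure with a CI is specified, and adjustment of the clinical and quality-of-life scores for their preoperative values is not specified.

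If separate intervals are all the reader has, the loss is substantial. At an assumed difference of 1.5 SD, the chance of seeing a difference is 39% with the 93.0% intervals, against 77% with a direct comparison. Part of that gap reflects the stricter error rate of non-overlap (about 1% against 5.0%). These figures rest on normal data, equal SD and complete data at 8 per arm. The gain from baseline adjustment rests on an assumed correlation of 0.5 to 0.7 and concerns secondary outcomes only.

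This weakens what the pilot can report and pass on to a larger trial. It does not invalidate the trial, and it should be corrected before analysis.

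**What to change.** - **Section 2.14, primary outcomes.** Name the between-arm difference at each visit as the primary estimate, labelled exploratory. Examples are the Hodges-Lehmann shift with its exact 95% CI, or the same on log counts reported as a ratio. Keep the per-arm medians as description.
- **Section 2.14, clinical scores.** For the Harris Hip Score and WOMAC, report the between-arm difference adjusted for the Visit 1 score. For Merle d'Aubigné grades and EQ-5D profiles, use rank or ordinal methods, since a Gaussian model does not suit them.
- **Section 2.15.** Remove the conflict between having no additional analyses and fitting a regression. Name the outcome and the treatment term, and limit the model to arm plus one or two named covariates, given 16 patients.

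The cost is a few rewritten sentences and a little more analysis work. No new data are needed. Recruitment was still in progress when the article was submitted, so on that timing the change could precede any analysis.

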### Methods for any additional analyses

2.15

Additional analyses are not planned. Nevertheless, an exploratory multivariate regression model will be constructed and adjusted for potentially important confounding factors such as age, gender, clinical baseline characteristics.

### Analysis population and missing data definition of analysis population relating to protocol nonadherence and any statistical methods to handle missing data

2.16

In the case of missing data, imputation will be made considering the treatment effects’ estimator is not biased and that an increase in type I error has been avoided. However, considering that the bone metabolic activity and bone morphology will be similar, and to ensure the trial's internal sensitivity in case of expecting a different evolution of one of the experimental groups, the last observation carried forward technique seems to be a conservative approach to the matter.

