Since the cement layer progressively attaches to the bone, a longitudinal evaluation must be performed. Risk of prosthetic loosening will be assessed according to the Harris Radiographic Loosening Risk Classification (Table S5, Supplemental Digital Content).[^10^,^11^]

Plain Radiographies will be assessed separately by 2 different physicians within the study team. In case of any discrepancies between their assessments, both physicians will discuss the plain radiographies until reaching a consensus. This consensus will be adopted as the final assessment.

Clinical outcomes of THA will be assessed by comparing patients’ pre- and postoperative answers to Harris Clinical Assessment scale (see Table S1, Supplemental Digital Content),[^12^,^13^] to Merle d’Aubigné Clinical Assessment Scale (see Table S2, Supplemental Digital Content),[^12^,^14^] and to Western Ontario and McMaster Universities Arthritis (WOMAC's Index) (Western Ontario and McMaster Universities Arthritis) (see Table S3, Supplemental Digital Content).^[15]^ Results in terms of quality of life will be assessed by comparing patients’ pre- and postoperative answers to the EuroQoL-5D-3L© questionnaire (see Table S4, Supplemental Digital Content).^[16]^

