### Outcomes

2.7

Study primary and secondary outcomes are summarized in Table 2.

**Table 2 T2:** Summarized primary and secondary study outcomes.

Primary outcomes
Bone metabolic activity: number of counts per image set (median and its 95% CI) in the SPECT study. *Note: Counts per image set are a measure unit defined as the number of photons captured by the gamma camera, which represent the radiopharmaceutical uptake.* *SPECT will be performed at 3, 6, 12, and 24 mo of the intervention.*
Bone morphology: Alignment angles (median and its 95% CI) in the plain radiography and in the CT scan study. *Note: Alignment angles will be measured in degrees using the anatomical axis of the femur as a reference. Stem deviations from the femoral anatomical axis will be classified as “Varus” (if the tip of the stem is situated laterally to the femoral anatomical axis) or as “Valgus” (if the tip of the stem is situated medially to the femoral anatomical axis).* *Plain radiography will be performed at baseline and at 3, 6, 12, and 24 mo of the intervention.* *CT Scan will be performed at 3, 6, 12, and 24 mo of the intervention.*
Secondary outcomes
Axial displacement (median and its 95% CI) in the plain radiography and in the CT scan study. *Note: Axial displacement will be measured (in millimeters) using the inter-teardrop line as a reference. In the CT Scan study, this inter-teardrop line will be measured on the coronal plane.* *Axial displacement will be assessed at 3, 6, 12, and 24 mo of the intervention.*
Prosthesis loosening risk: number (and proportion) of patients classified as “possibly loose”, “probably loose”, and “definitely loose”, according to the Harris Radiographic Classification of Loosening Risk. *Note: Possibly Loose: Presence of a radiolucent line of 50% to 99% of the cement-bone boundary; Probably Loose: Radiolucency line at 100% of cement-bone boundary; Definitely Loose: Stem migration or a fracture of the cement mantle.*
Clinical outcomes: Harris Hip Score (median and its 95% CI). *Note: Being a score of 100 points the best possible result, and a score of 0 the worst possible result.*
Clinical outcomes: Merle d’Aubigné Score (median and its 95% CI) *Note: Clinical grades (Very good, Good, Medium, Fair, Poor) are given by the scores of Pain and Walking ability and adjusted down 1 to 2 grades, depending on the mobility score.*

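### Last observation carried forward is called conservative, but it is not reliably so for outcomes expected to change between 3 and 24 months

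*Protocol article*

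**What the plan says.** Section 2.16 sets a condition for any imputation: that the treatment-effect "estimator is not biased and that an increase in type I error has been avoided". It then turns to one technique and says that "the last observation carried forward technique seems to be a conservative approach to the matter". Two reasons are given in the same sentence. One is a premise, "considering that the bone metabolic activity and bone morphology will be similar". The other is protection "in case of expecting a different evolution of one of the experimental groups".

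Elsewhere the protocol describes its subject as change over time. Section 1.1 motivates the trial by noting that "there are no studies comparing bone metabolism evolution in the postoperative period between these 2 approaches". Table 2 states for the first primary outcome that "SPECT will be performed at 3, 6, 12, and 24 mo of the intervention", and neither Table 2 nor the visit schedule in Table 3 contains a preoperative SPECT. Section 2.14 summarises SPECT counts by the median and its 95% CI in order "to assess whether there are bone metabolic differences between the 2 types of cemented stem prostheses", and summarises the clinical scores before and after surgery.

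**The concern.** Carrying a value forward assumes that a patient's result stays where it was at the last attended visit. A trial set up to describe how bone metabolism evolves over two years cannot take that for granted, and clinical scores after hip replacement are compared before and after surgery because they are expected to move.

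The justification is also circular. It presumes that the stems behave alike, which the trial is meant to find out. It then allows that one group may evolve differently, a case in which carrying forward can distort the comparison.

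At stake are the 12- and 24-month medians. With 8 patients per arm, two carried values are a quarter of the arm, and measurements from month 3 or 6 would be presented as 24-month data. The method also has a gap of its own: a patient who misses the month-3 SPECT-CT has no earlier scan to carry.

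**Working it through.** The protocol derives no figure for missing data, so there is nothing to reproduce. It gives no uptake trajectory, variance, correlation or dropout rate. All of these are assumed below, and the results are illustrations only.

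**Inputs from the protocol:** 8 patients per arm (section 2.8); SPECT at 3, 6, 12 and 24 months (Table 2); the median as summary (section 2.14); withdrawal possible at any time (section 2.4).

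**Assumed:** lognormal uptake with CV 30%, so the log-scale variance is ln(1 + 0.30²) = 0.086; within-patient correlation 0.7; mean uptake 1 at month 3 and 1 − d at month 24, with d = 0.20, 0.40 or 0.60; patients lost after month 3 independently of their outcome.

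**1. Creating a difference.** There is no true difference, and 2 of 8 against 0 of 8 are carried from month 3. At d = 0.40 the affected arm's 24-month median rises from 0.60 to 0.666, and 0.666/0.60 = 1.11.

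| Decline | Ratio of 24-month medians (truth 1.00) | Ratio of geometric means, (1/(1 − d))^(2/8) |
|---|---|---|
| 20% | about 1.05 | (1/0.8)^0.25 = 1.06 |
| 40% | about 1.11 | (1/0.6)^0.25 = 1.14 |
| 60% | about 1.13 | (1/0.4)^0.25 = 1.26 |

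The middle column is the one that matches the planned summary. The median levels off because two high carried values only move it from between the 3rd and 4th to between the 4th and 5th of the six true late values.

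**2. Masking a difference.** The arms are equal at month 3, the true 24-month ratio is 0.70, and the reference arm declines by 40%. With 3 of 8 carried in each arm the medians are about 0.532 and 0.715, so the ratio is 0.532/0.715 = 0.74. With 2 of 8 per arm it is about 0.71. On geometric means, 3 of 8 would give 0.70^(5/8) = 0.80, but that is not the planned summary.

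**3. Equal losses.** With 2 of 8 against 2 of 8, the same trajectories and no true difference, the ratio of medians is 1.00. A 5% t-test on the log scale rejects about 1.4% of the time at a 40% decline. With 2 against 0 it rejects about 8%, and with 1 against 0 about 4 to 5%.

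**4. A second set of assumptions.** Here values are in units of the between-patient SD, the correlation is 0.6, both arms have means 3, 2, 1 and 0 at the four visits, and month-6 values are carried to month 24.
- One, two or three carried values of 8 raise an arm's 24-month median by 0.16, 0.37 or 0.64 SD.
- Losses of 2 against 0 create a false difference of 0.37 SD; 3 against 1 create 0.48 SD.
- With a true difference of 1.00 SD (the slower arm at 3, 2, 1.5 and 1), the result is 0.86 at 2 against 2. It is 0.63 when the two losses fall only in the faster-declining arm, and 1.24 when they fall only in the slower one.
- With flat trajectories there is no bias.
- Observed values alone gave about 0.00 and 1.00 where those were the truth, because losses were assumed unrelated to outcome.

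**The case against.** Several points on the other side have force.

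- **The wording is tentative, and the trial is a 16-patient exploratory pilot.** Section 2.14 gives descriptive medians and intervals and names no test or alpha. That stands. The rejection rates above belong to tests supplied for illustration, and the harm is a misleading late estimate rather than a failed confirmatory claim.
- **Carrying forward can be conservative.** That also stands: with equal losses and equal trajectories the comparison is unbiased and the test rejects too rarely. A reader might infer that the method always breaks both of the conditions in section 2.16. It does not. It fails to guarantee them, and the plan gives no reason to expect the favourable case.
- **Not every outcome is shown to change.** A reader might take "Since the cement layer progressively attaches to the bone, a longitudinal evaluation must be performed" in section 2.3 as proof that all outcomes evolve. That sentence introduces the assessment of loosening risk and gives no uptake trajectory. Change is well supported for SPECT uptake by the stated aim, and for the clinical scores by the comparison before and after surgery. Nothing shows a trend in alignment angle, the other primary outcome, which may be nearly constant.
- **Losses may be few.** Sections 2.5, 2.9 and 2.12 describe reminders, scheduling calls and scans on routine visit days. With no missed visits there is no bias, and 2 of 8 against 0 after the first scan is an unfavourable pattern. This limits the likely size of the effect but does not make the stated rule sound.

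**Conclusion.** The concern holds in a limited form. Section 2.16 chooses a technique, calls it conservative on a premise that is itself the study question, and does not reconcile it with its own condition of no bias. For uptake and clinical scores the technique is not reliably conservative: it can create, shrink or exaggerate a late difference, depending on who is lost and when.

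Under the assumptions above, the spurious ratio of 24-month medians is about 1.05 to 1.13 with 2 of 8 against 0 carried, and a true ratio of 0.70 becomes about 0.74 with 3 of 8 carried per arm. Larger figures, such as 1.26 or 0.80, are geometric-mean results and should not be read as effects on the planned medians. Direction and size depend on trajectories and losses that the protocol does not give.

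This should be corrected before analysis, but it does not undermine the trial. The lack of any value to carry when the month-3 SPECT is missed does not depend on the assumed figures.

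**What to change.** Remove last observation carried forward as the default in section 2.16, together with the statement that the groups will be similar. At each visit, report observed-case medians with 95% CI by arm and the number of patients contributing.

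A likelihood-based repeated-measures model on all observed visits could be added as support. It needs no imputation and is valid if data are missing at random, but it is optional: for uptake on the log scale it changes the summary to geometric means, and it adds distributional assumptions in 16 patients. If carrying forward is kept at all, label it a sensitivity analysis and say how a missed month-3 SPECT is handled.

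The cost is an amendment to the analysis text and somewhat wider late-visit intervals, which reflect the data actually lost. Observed-case medians rely on missingness being unrelated to outcome, so reasons for missed visits should be listed by arm. If only 5 patients remain in an arm, the full range as a distribution-free interval for the median covers 1 − 2 × 0.5⁵ = 93.75%, so the actual coverage should be stated.
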